### Outcomes

2.7

Measurements of BP (primary outcome) and heart rate will be performed before, during (every 5 minutes), and at the end of each session, being measured again in the follow-up.

Blood will be collected from all participants to measure the dosage of IL-6, CRP, and NO. Collection will be performed at the beginning of the study and before each cycle (BASELINE—B1, B2, B3), at the end of each cycle of photobiomodulation (END—E1, E2, E3) and 1 month after the end of the proposed therapy (FL-UP). In total, there will be 7 samples from each patient.

Serum samples will be collected in two 10 mL dry tubes and will be processed in a centrifuge at 1000 rpm for 5 minutes and the plasmas at the top of the tubes will be withdrawn and centrifuged again to obtain clear plasmas. The samples will be stored in a freezer at −80° C until the analyses are performed.

The CRP analysis will be performed by means of the immunoturbidimetric test, which allows the quantification of the CRP concentration present in the sample when following the protocol established by the kit manufacturer. IL-6 analysis will be performed via the ELISA method with the use of a specific kit (Human IL-6 ELISA MAX Deluxe, BioLegend, San Diego). The concentration of NO will be determined using a specific kit (Total NO and Nitrite/Nitrite Parameter Assay Kit), where nitrite/nitrate concentration will be determined via the Griess reaction after enzymatic reduction of nitrate in nitrite with the nitrate reductase enzyme in a reduction solution. This procedure will be in accordance with those recommended by the manufacturers.

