Currently, the treatment of hypertension is based on a nonpharmacological and pharmacological combination, aimed at implanting strategies that may reverse or prevent the progression of these factors, as well as the prescription of drugs with vasodilatory actions, beta blockers, and diuretics, leading to a decrease in BP.^[11,16]^ It should be emphasized that the use of drugs can cause the manifestation of signs and symptoms which are the result of adverse or collateral effects. This in turn may influence the patient's adherence to treatment, which consists in the acceptance of and obedience to what was prescribed and directed by the attending healthcare professional.^[17]^ Non-adherence is identified as the main cause of uncontrolled arterial hypertension ^[18]^ therefore it becomes imperative to find methods which facilitate this process with the purpose of promoting improvement in the quality of life of these patients.

Low intensity laser therapy, or photobiomodulation, is capable of inducing a photobiological response inside the cells; activating the production of adenosine triphosphate (ATP), NO, and reactive oxygen species; and altering sodium–potassium pumps and calcium channels in cell membranes, ^[19]^ as well as proving to be an efficient, noninvasive, low cost, safe tool.

Among the different methods of photobiomodulation, intravascular laser irradiation of blood (ILIB) has been shown to prompt systemic effects. ILIB has been studied since 1981 by Soviet scientists; it was developed for the treatment of cardiovascular diseases with evidence of improved blood rheological properties and microcirculation as well as reduction in the infarct area, cardiac arrhythmias, and sudden death. ^[20]^

In view of the above, the verification of the effects of systemic photobiomodulation on the control of BP in humans shows itself to be a current, relevant, promising area of study, principally in order to prevent patients’ health problems and the consequent high cost to public health, along with minimizing the gaps in the literature in this area.

Will be a study single-center, controlled, randomized, blinded clinical trial whose general objective will be to evaluate the effects of systemic photobiomodulation on the hemodynamic variables of hypertensive patients (the primary outcome variable will be BP values). Besides, will be analyzed the dosages of IL-6, CRP, and NO.

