### Group composition and randomization: (recruitment and randomization)

2.6

Recruitment will be carried out respecting Resolution 466/2012, which regulates human research in Brazil. The patients recruited will have their multiprofessional charts analyzed for demographic and descriptive characterization of the sample.

Nursing consultations in the form of a home visit, or not—at the discretion of the participant, will be scheduled to give healthcare guidance, for an initial interview, completion of the clinical file, and realization of hemodynamic and anthropometric measurements, as well as blood collection and photobiomodulation interventions.

For the application of the photobiomodulation, the participant will place a bracelet where the tip of the coupled laser equipment will be positioned on the radial artery.

We will use the randomization mechanism provided by Sealed Envelope Ltd. (London, UK)^[22]^ Participants will be randomized into blocks of 8 individuals, comprising 4 study groups. They will be identified by sequential numbers, according to the order of recruitment. Immediately before starting treatment, the researcher will look at the randomized list and, using their identification number, verify which group the participant belongs to. The patient will not know to which group he or she has been allocated; only the researcher who will do the irradiations will know. The analysis of the data will be performed by a third person who will also not know group allocations.

A schematic diagram of time schedule of enrolment and interventions of the research groups is summarized in Figure 1.

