During the study, strategies will be follow to improve adherence to intervention protocols, as nursing consultations in the form of a home visit, or not—at the discretion of the participant. In addition, patients who have a prescription for drug therapy should not suspend it. All patients, regardless of pharmacological or nonpharmacological use, will receive guidelines for the nonpharmacological treatment of hypertension, focusing on the need to maintain a healthy lifestyle, minimizing risk factors for hypertensive disease. These orientations include directions for healthy eating with decreased levels of sodium, fat, and sugar; regular physical exercise with the supervision of a professional; the need for quality sleep of at least 6 to 8 hours; abandonment or diminution of smoking; and the need for stress-minimizing leisure. Patients taking medication will have guidelines regarding the adequate use of medications, respecting the dose and prescribed schedule, reinforced.

Patients have autonomy for discontinue interventions and in this case, they will be replaced, but the same allocation will be remaining. Any outcome data collected from patients will be disconsidered and the participants will remain in ambulatory care.

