### Procedure for data collection, blinding, and photobiomodulation

2.8

A researcher will generate the allocation sequence using the Sealed Envelope Ltd. An examiner will enroll and assign participants to interventions, performing anthropometric assessments, measurement of hemodynamic variables, and blood collection. Other one will be trained to perform the photobiomodulation and will process the blood samples. Other researcher will perform the statistical analyzes of the results without having participated in the collection of data or the application of the procedures. In this way, the last researcher and the patients will be blind. Only after the end of the trial, the participants will know the allocation and results.

A data collection instrument was developed to contain the information needed to achieve the proposed objectives. The variables will be addressed in categories: characterization of the sample, evaluation of risk factors for cardiovascular disease, anthropometric data, data referring to BP measurements, heart rate, biochemical markers before and after photobiomodulation, as well as approach to the use of medicines, diet, and complementary information.

The photobiomodulation will be applied using the Therapy XT laser equipment, brand DMC, Brazil, following the parameters described in Table 1.

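### The outcome called NO is total nitrite plus nitrate, so a within-group change in it cannot be credited to the laser; conclusions should rest on laser versus sham

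*Protocol article*

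**What the plan says.** - **Label.** Section 2.7: "The concentration of NO will be determined using a specific kit (Total NO and Nitrite/Nitrite Parameter Assay Kit".
- **Assay.** The same sentence goes on to say that "nitrite/nitrate concentration will be determined via the Griess reaction after enzymatic reduction of nitrate in nitrite with the nitrate reductase enzyme".
- **Rationale.** The Introduction says that photobiomodulation works in the cell by "activating the production of adenosine triphosphate (ATP), NO, and reactive oxygen species".
- **Draws.** Section 2.7 ties the samples to study phase: "Collection will be performed at the beginning of the study and before each cycle (BASELINE—B1, B2, B3", then the end of each cycle and one month after therapy, seven in all. The article gives no condition on food or time of day.
- **Guidance.** Section 2.6: "All patients, regardless of pharmacological or nonpharmacological use, will receive guidelines for the nonpharmacological treatment of hypertension". On diet, "These orientations include directions for healthy eating with decreased levels of sodium, fat, and sugar"; exercise, sleep, smoking and leisure are covered too. The consultations for guidance are also those for blood collection: "Nursing consultations in the form of a home visit, or not—at the discretion of the participant, will be scheduled to give healthcare guidance".
- **Recorded data.** The collection form in section 2.8 includes "approach to the use of medicines, diet, and complementary information".
- **Analysis.** Section 2.9 plans parametric or nonparametric tests of differences between and within groups at α = 0.05. It does not say which comparison carries the conclusion.

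**The concern.** NO is measured because the laser is expected to raise its production. The assay turns nitrate into nitrite and reads the total, so nitrate from any source counts. Two things follow.

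First, the quantity reported is not the quantity named. Second, it can move for reasons unrelated to the laser. Every participant is advised on lifestyle during the study, and the article does not fix whether that advice comes before or after the B1 sample. A change from B1 to a later sample in a laser group could therefore reflect altered habits. Because section 2.9 gives within-group tests the same standing as between-group tests, such a change could be published as NO release caused by the laser.

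**Working it through.** **Inputs from the article:** four groups of 11; a sham group for each laser schedule; α = 0.05 (taken as two-sided); within- and between-group tests. The article gives no planning figure for NO. The 44 in section 2.3 was sized for BP, and the mean and SD behind it are not printed, so it cannot be recomputed. Nothing here rests on it.

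**Inputs assumed, because the article gives none:** the size of any diet-related shift over time (0, 0.5 or 1 SD of the change), and the share *s* of NOx variance due to diet (0 to 0.9).

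**Step 1: false attribution.** Simulate 20,000 trials with no laser effect and the same shift in the laser and sham groups, 11 per group. Test the laser group's change against zero (one-sample t) and laser against sham (two-sample t).

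| Shared shift (SD of change) | Laser vs sham, % significant | Within laser group, % significant |
|---|---|---|
| 0 | 4.9 | 4.8 |
| 0.5 | 5.2 | 31.9 |
| 1 | 5.0 | 84.6 |

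The randomised contrast keeps its 5% level and the within-group test does not. Setting two within-group tests side by side does not repair this. With independent groups, the chance that the laser group is significant and its sham is not is 0.319 × (1 − 0.319) = 0.22 at a 0.5 SD shift, and 0.846 × (1 − 0.846) = 0.13 at 1 SD.

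**Step 2: precision.** Diet variation shared by the groups inflates the SD, so a standardised effect d₀ becomes d₀ × √(1 − s). With 11 versus 11, 95% power (noncentral t, 20 df) needs d₀ = 1.617. At s = 0.5, d = 1.617 × √0.5 = 1.143.

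| s | d | Power | Required n per group, multiplied by 1/(1 − s) |
|---|---|---|---|
| 0 | 1.617 | 0.95 | 1.00 |
| 0.10 | 1.534 | 0.93 | 1.11 |
| 0.25 | 1.400 | 0.88 | 1.33 |
| 0.50 | 1.143 | 0.72 | 2.00 |
| 0.75 | 0.809 | 0.44 | 4.00 |
| 0.90 | 0.511 | 0.21 | 10.00 |

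This takes one comparison of one draw per person. Combining several draws would average out day-to-day food variation and soften the loss.

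**The case against.** A reader might go further and infer that the outcome mostly measures food and hardly any laser-induced NO. The documents do not support that. They give no dietary share of NOx, and step 2 runs from a trivial loss to a severe one depending on a share that nobody has stated.

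Several other replies also have force:

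- **The design protects the main comparison.** Each laser schedule has its own randomised sham, patients are blinded and all receive the same guidance. Step 1 confirms that a shared shift leaves the laser-sham test at its nominal level. This stands in full.
- **Silence on fasting is not an error.** A condensed article commonly leaves such sampling detail to the full protocol or a laboratory manual. This stands, and the point does not depend on it.
- **The guidance does not mention nitrate.** The stated dietary content is sodium, fat and sugar. A shift in NOx from this advice is possible, not shown.
- **The assay is disclosed.** The sentence that names NO also says that nitrite and nitrate are determined, so the naming issue is partly editorial. Nor does the article define the endpoint as NO from the vessel wall; the Introduction speaks of production in cells.

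None of these replies answers the remaining problem. Tests within and between groups are planned on an equal footing, for a marker that other sources can move.

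**Conclusion.** The point holds in a limited form. The outcome is NOx, an indirect marker that cannot tell its sources apart. A within-group change in it does not show a laser effect; the difference between a laser group and its own sham can. Shared diet variation costs the randomised contrast precision but does not bias it.

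The sizes (32% and 85% false attribution; power falling from 0.95 to 0.72 or lower) rest on assumed shifts and shares, and only the direction follows from the design. The matter is minor: NO is not the primary outcome, and neither BP nor the 44 participants is affected.

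**What to change.** 1. **Name (2.7).** Call the outcome total nitrite/nitrate (NOx) and describe it as an indirect marker of NO.
2. **Inference (2.9).** Base the conclusion on Laser 60 versus Placebo 60 and Laser 30 versus Placebo 30, each adjusted for B1. Report within-group changes as descriptive, without a claim of effect.
3. **Sensitivity analysis.** Use the diet and medicine data already on the form to repeat the comparison. Keep this secondary, because those entries may be made after randomisation.
4. **Draw conditions (2.7).** Take each participant's samples at a consistent time of day and record recent food intake, or state the conditions already in force.

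Any fasting condition around sessions must first be reconciled with section 2.8, which anticipates a fall in BP with possible lipothymia. This review proposes no such condition.

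The cost is a few sentences, some scheduling care and an entry for recent food. No extra draws, assays or staff are needed.

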### Procedure for data collection, blinding, and photobiomodulation

2.8

A researcher will generate the allocation sequence using the Sealed Envelope Ltd. An examiner will enroll and assign participants to interventions, performing anthropometric assessments, measurement of hemodynamic variables, and blood collection. Other one will be trained to perform the photobiomodulation and will process the blood samples. Other researcher will perform the statistical analyzes of the results without having participated in the collection of data or the application of the procedures. In this way, the last researcher and the patients will be blind. Only after the end of the trial, the participants will know the allocation and results.

A data collection instrument was developed to contain the information needed to achieve the proposed objectives. The variables will be addressed in categories: characterization of the sample, evaluation of risk factors for cardiovascular disease, anthropometric data, data referring to BP measurements, heart rate, biochemical markers before and after photobiomodulation, as well as approach to the use of medicines, diet, and complementary information.

The photobiomodulation will be applied using the Therapy XT laser equipment, brand DMC, Brazil, following the parameters described in Table 1.

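### Sections 2.6 and 2.8 disagree on who learns the allocation, so neither concealment from the enroller nor blinding of the blood pressure assessor is secured

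*Protocol article*

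**What the plan says.** Section 2.6 (Group composition and randomization) describes the allocation step. Randomization is in blocks of 8 across the 4 groups, and each participant gets a running number as he or she is recruited. On how the group is then found, the section says: "Immediately before starting treatment, the researcher will look at the randomized list and, using their identification number, verify which group the participant belongs to". It adds that the patient does not know the group, that "only the researcher who will do the irradiations will know", and that the data analyst is also unaware of it.

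Section 2.8 (Procedure for data collection, blinding, and photobiomodulation) divides the work among four people. One generates the sequence. The second is the examiner: "An examiner will enroll and assign participants to interventions, performing anthropometric assessments, measurement of hemodynamic variables, and blood collection". The third is the operator: "Other one will be trained to perform the photobiomodulation and will process the blood samples". The fourth does the statistics. The section concludes: "In this way, the last researcher and the patients will be blind".

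Section 2.7 makes blood pressure the primary outcome. It is measured before, every 5 minutes during and at the end of each session, and again at follow-up.

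**The concern.** Someone who assigns participants to interventions ordinarily knows the intervention. Section 2.8 gives that task to the examiner and irradiation to someone else, so the examiner falls outside the one role that section 2.6 allows to know. The same examiner decides who enters and takes the primary outcome.

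Two protections depend on how this is resolved. If the enroller knows or can predict the next group, the choice and timing of who is enrolled can depend on it (selection bias). If the assessor knows the group, repeat readings, their timing and their recording can depend on it (detection bias). A larger sample removes neither, and nor does a blinded statistician. The trial is described as blinded in the Introduction and in section 2.1, and a reader needs to know whether that covers the person measuring the primary outcome.

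**Working it through.** **1. The roles side by side**

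| Question | Section 2.6 | Section 2.8 |
|---|---|---|
| Who reads or makes the assignment? | The researcher, from the list, just before treatment; in context, the operator | The examiner |
| Who knows the group? | The operator only | Not stated directly; the examiner assigns |
| Who is named as unaware or blind? | Patient and analyst | Patients and statistician |
| Who measures blood pressure? | Not stated | The examiner |

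The examiner and the operator are different people in section 2.8, so the first two rows conflict. In the third row neither section names the examiner. The article describes no barrier between the list and the examiner. Sequence generation is a separate role and is not at issue.

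**2. How much of the primary outcome is exposed**

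Inputs: the session schedules in section 2.6 and the measurement rule in section 2.7. I count the last 5-minute reading as the end-of-session reading.

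- 60-minute schedule: 3 cycles × 5 days = 15 sessions. Readings per session: 1 before + 11 during + 1 at the end = 13. Total 15 × 13 = 195 per participant.
- 30-minute schedule: 3 × 10 = 30 sessions. Readings per session: 1 + 5 + 1 = 7. Total 30 × 7 = 210 per participant.

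Most of these readings fall while the device is running. The placebo obturator sits at the laser output. The article says that the equipment noise is unchanged, but not that the obturator is out of the examiner's view.

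**3. Predictability in blocks of 8**

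Inputs: block size 8 and 4 groups (section 2.6), 44 participants (section 2.3; 4 × 11 = 44). Assumptions: two places per group in each block; the enroller knows the block size, sees every past assignment and guesses a group with the most places left. The list itself stays hidden.

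The chance of a correct guess at each place is the largest number of places left in any group, divided by the places left in the block, averaged over what can have happened:

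- Places 1 to 4: 2/8, 2/7, 2/6, 2/5 = 0.250, 0.286, 0.333, 0.400.
- Place 5: the 4 remaining are all different with probability 16/70 = 0.229, so 0.771 × 2/4 + 0.229 × 1/4 = 0.443.
- Place 6: the 3 remaining are all different with probability 32/56 = 0.571, so 0.429 × 2/3 + 0.571 × 1/3 = 0.476.
- Place 7: the 2 remaining are the same group with probability 4/28 = 1/7, so 1/7 × 1 + 6/7 × 1/2 = 0.571.
- Place 8: 1.

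The sum per full block is 3.760. Since 44 = 5 × 8 + 4, the total is 5 × 3.760 + (0.250 + 0.286 + 0.333 + 0.400) = 18.80 + 1.27 = 20.07 correct guesses. 20.07/44 = 45.6%, against 11/44 = 25% by chance.

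Certain allocations: place 8 always and place 7 with probability 1/7, so 5 × (1 + 1/7) = 5.7 of 44. A simulation of 3,000 lists agrees (45.5% and 5.71). If the examiner could read the list, all 44 would be known, but the article does not say that the examiner can.

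**The case against.** The strongest reply is that section 2.6 already describes a sound procedure. The participant is recruited and numbered first, the list is consulted only just before treatment, and the operator alone learns the group. On that text, concealment and assessor blinding could both survive. Assigning in section 2.8 might mean no more than giving out the next sequential number. This reply stands as far as it goes: it shows a good plan may be intended. It does not explain why section 2.8 leaves the examiner out of its explicit list of blinded roles, and it requires reading assignment to an intervention as something else.

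Four stronger readings are tempting, and the article does not support them.

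- **That both protections are already lost.** This holds only if section 2.8 overrides section 2.6, and nothing says that it does.
- **That the examiner handles an open list.** Section 2.6 mentions the list but not the examiner; section 2.8 mentions the examiner but not the list.
- **That the biomarker assays are compromised because the operator processes the blood.** Section 2.7 uses that word for centrifugation before freezing. Nobody is named as running the assays, and they are not the primary outcome.
- **That the bias is a given share of the treatment effect.** Section 2.3 prints no effect or standard deviation, and the blood pressure device is not named. An automated device would reduce reading bias, though not influence over repeats or timing.

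It is also fair that the article says blinded, not assessor-blinded, that it states openly who is blind, and that the sham is concrete.

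**Conclusion.** The concern holds as a contradiction between two sections and a gap in who is declared blind. As written, neither concealment of the allocation from the enroller nor blinding of the primary-outcome assessor is secured. This is more than brevity in an article, because section 2.8 positively gives enrolment, assignment and blood pressure measurement to one person.

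The size of any bias in blood pressure cannot be derived from the document. The predictability figures (about 46% guessable, about 6 of 44 certain) are conditional: they apply to an enroller who knows the block size and sees every past assignment, which section 2.6 would prevent and section 2.8 would allow. Confidence is high for the inconsistency, and does not extend to any claim that bias has occurred. The point must be settled before enrolment, since it cannot be repaired in the analysis.

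**What to change.** Reconcile sections 2.6 and 2.8, using the four roles already described:

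1. In section 2.8, let the examiner enrol and measure, and remove the assigning of participants from that role.
2. State that the examiner has no access to the randomization list.
3. State that only the irradiation operator opens the allocation, after enrolment is complete and baseline blood pressure is recorded.
4. State that the operator sets the obturator out of the examiner's sight.
5. Add the blood pressure examiner to those named as blind, specifying laser versus placebo within each session schedule. The 30- and 60-minute schedules cannot be masked from someone present, so the claim should not go further.

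No extra staff are needed. The cost is a few sentences and the discipline of keeping operator and examiner apart at each session. With 11 participants per group that is 22 × 15 + 22 × 30 = 990 planned sessions, some possibly at participants' homes, so the arrangement should be workable there too. One limit remains: the examiner will see which schedule each participant follows, so the schedule of a late place in a block can still be guessed, but not whether it is laser or placebo.

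### Blood processing for IL-6, CRP and NO is given to the irradiating researcher, the one person who by the protocol's own account knows the allocation

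*Protocol article*

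**What the plan says.** Section 2.6 (group composition and randomization) describes how the allocation becomes known: "Immediately before starting treatment, the researcher will look at the randomized list and, using their identification number, verify which group the participant belongs to". On who holds that knowledge, it says "only the researcher who will do the irradiations will know".

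Section 2.8 (data collection, blinding and photobiomodulation) divides the work. A first role enrols, measures and draws blood: "An examiner will enroll and assign participants to interventions, performing anthropometric assessments, measurement of hemodynamic variables, and blood collection". A second role gives the laser and has a further task: "Other one will be trained to perform the photobiomodulation and will process the blood samples". A further researcher does the statistics. The section then states who is blinded: "In this way, the last researcher and the patients will be blind".

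Section 2.7 (outcomes) explains what the blood is for: "Blood will be collected from all participants to measure the dosage of IL-6, CRP, and NO". It also gives the number of collections: "In total, there will be 7 samples from each patient". These are three cycle baselines (B1 to B3), three cycle ends (E1 to E3) and the follow-up. In that section, processing means centrifugation, withdrawal of plasma and a second spin. Storage and the three assays follow in sentences that name no operator.

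**The concern.** The person who knows whether a participant received laser or placebo also prepares that participant's blood for three outcomes. The article states this division of roles outright, so it is not a detail left to a fuller document. The processor is not among those listed as blind.

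Some steps before the assay depend on the operator. The article sets no time from draw to spin, and how much plasma to withdraw and when it counts as clear are matters of judgement. If laser and placebo samples were handled differently, the difference would enter the marker values before any analysis. A blinded statistician could neither detect it nor remove it. The trial presents itself as blinded, and IL-6, CRP and NO are its only blood-based evidence on mechanism.

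**Working it through.** The plan gives no figure to reproduce on this point. The check compares the role statements and then counts samples.

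**Roles**

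| Role | Task in 2.8 | Knows the group? |
|---|---|---|
| Examiner | Enrols and assigns, measures, draws blood | No under 2.6, but the word for assigning in 2.8 leaves doubt |
| Irradiating researcher | Gives the laser, processes the blood | Yes (2.6) |
| Statistical researcher | Analyses | No (2.6 and 2.8) |
| Patient | None | No (2.6 and 2.8) |

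Processing falls to the only role in this table that 2.6 names as unblinded.

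**Would the participant number mask the tubes?** No. Section 2.6 has the researcher consult the list "using their identification number, verify which group the participant belongs to". The number is the key to the group, so a tube carrying it is readable to anyone who holds the list. The article does not say how tubes are labelled and describes no other identifier.

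**Count of samples** (44 participants from 2.3, 7 samples each from 2.7)

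- By role: 44 x 7 = 308.
- Certainly after the look-up: 44 x 6 = 264. B1 is drawn at the start of the study and the list is read just before treatment starts, so the 44 B1 tubes could be spun before the group is known. The article does not fix that order.

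**Illustration of size.** The article gives no marker variances, so the SD and the handling difference below are assumptions.

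- Assumed SD on the log scale: 0.5 to 0.8. Assumed systematic handling difference between two arms: 10%.
- SE of a log ratio with 11 per arm = SD x sqrt(2/11). This is 0.5 x 0.426 = 0.213, and 0.8 x 0.426 = 0.341.
- Shift in SE units = ln(1.10)/SE. This is 0.095/0.213 = 0.45, and 0.095/0.341 = 0.28.
- False-positive rate of one two-sided 5% test = P(|Z + shift| > 1.96) = 0.073 for SD 0.5 and 0.059 for SD 0.8.

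Under these assumptions the nominal 5% becomes about 6% to 7%.

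**The case against.** **The assays are not assigned to this person.** A reader might infer that the irradiating researcher also controls plate layout, re-runs and result reading, so that all 308 x 3 = 924 marker results are produced unblinded. The article does not support that. Section 2.7 uses processing for spinning and separation and names nobody for the assays. This objection stands, and the point is limited to sample handling.

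**Not every sample is certainly handled with knowledge of the group.** This stands for the 44 B1 samples. It does not touch the other 264.

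**The room for differential handling is narrow.** Section 2.7 fixes the spin speed and time, a second spin and the storage temperature, and the assays are quantitative and follow manufacturers' instructions. Most of this stands. It leaves open the delay before spinning and the judgement on withdrawal and clarity.

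**A common handling difference would cancel in within-patient change.** This is true if it affects baseline and later samples alike, and the illustration above ignores it. It would not cancel if B1 were spun before the look-up and the difference arose only afterwards.

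**Tube coding is a detail an article may omit, and laboratory blinding is never claimed.** Both are true, and missing coding is not the point. The point rests on the stated assignment of processing to the unblinded person.

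**A code alone would not mask a fresh tube.** Someone who has just irradiated a participant can recognise that participant's sample by its timing. This stands, and it is why the remedy has to move the processing step as well as code the samples.

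**Conclusion.** The point holds in limited form. Sections 2.6 and 2.8 together give blood processing to the person who knows the allocation: 308 samples by role, at least 264 of them after the look-up. Unblinded assay reading is not shown.

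The likely effect is small. Blood pressure is the primary outcome and the three markers are secondary and measured with standardised tests. Even an assumed 10% handling difference, with assumed log-scale SDs of 0.5 to 0.8, moves the false-positive rate of a single test only from 5% to about 6% to 7%. No such difference is known to occur. The severity is minor, and the point is worth making because the change is cheap.

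**What to change.** Amend section 2.8 as follows.

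1. The examiner who draws the blood, and who under 2.6 does not know the group, also spins and aliquots the samples. The irradiating researcher no longer processes them.
2. The examiner labels each aliquot with a code unrelated to the participant number and keeps the code list.
3. Whoever runs the assays works on coded aliquots only, with all 7 samples of a participant on one plate where the assay uses plates.
4. The code list is released after the assay file is locked.
5. Reconcile the statement in 2.8 that the examiner will assign participants with the statement in 2.6 that only the irradiating researcher knows the group. The fix depends on the examiner having no access to the randomised list.

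The cost is a few sentences in 2.8, somewhat more work for the examiner and a second code list to keep. No extra staff are needed, and the sample size, visits and treatment do not change.
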